### Phase 3: post family care conference data collection

Phase 3 will take place approximately 6–8 weeks after phase 2. We will collect post family care conference data for the DCS, FPCS, CSRI and FAST measures. We will undertake follow up interviews with external facilitators, internal facilitators, nursing home managers, other staff not delivering the intervention and family carers to further explore barriers and facilitators to implementation.

### Economic aspects of implementation

An important feature of this evaluation will be to understand the level of resource available and required to permit the implementation of the intervention in each site and country. The inputs used to implement the intervention will be collected and reported on a per-site, per-country basis, and indicative costs calculated. The interviews in phase 1 and 3 will be used to better understand the factors that drive resource use and variation between care homes and partner countries.

### Data collection delivery methods

The methods of delivery for data collection will be flexible in order to accommodate and be sensitive to the needs of the different participant groups and individuals in this study. It is important to be flexible given each individual will be participating in a different regional and national context, and possibly with Covid-19 social distancing measures in place in nursing homes. For example, interviews in the study may be undertaken in-person, by telephone or on MS Teams (GDPR compliant). Questionnaires will be able to be completed in-person, over the telephone or returned by post.

### Data management and analysis

Within each nursing home, data will be analysed a) within data set (nursing home), followed by a b) cross-case analysis. The domains; Effectiveness, Adoption, Implementation, and Maintenance, will be assessed through quantitative descriptive indicators and qualitative interviews with both nursing home staff and family members.

All interviews will be digitally recorded and transcribed verbatim. We will analyse qualitative data in NVIVO and follow the framework analysis style outlined by Ritchie and Spencer [31]. This will be informed by the analysis of qualitative data, for which we will develop codebooks for each participant group and time point in the study. These codebooks will be developed in collaboration with researchers from each partner country following analysis of the first two interviews in each country. The analytical process using the codebooks will drive two higher level analytical processes. Firstly, they will be used in conjunction with the nursing home profile to develop an individual site template to develop a case-by-case analysis. This will also include the quantitative data. Descriptive statistics will be used to analyse the quantitative data collected from the DCS and FPCS and will be used to triangulate the qualitative data. Secondly, the codebooks and the individual site templates will inform the development of a cross-case framework to further summarise and synthesise data by generating themes, patterns, and interrelationships in an interpretive fashion.

During the analysis we will compare the pooled outcome measure data from the current adapted Family Carer Decision Support intervention to the outcome measure data that was collected as part of the earlier cluster randomized control trial involving 24 nursing homes located in Northern Ireland [20]. This will determine how the adapted implementation approach for scaling up the intervention compares to the original implementation approach.

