This approach to advance care planning has been subject to previous research. The initial Family Carer Decision Support study employed a cluster randomized control trial involving 24 dementia care nursing homes located in Northern Ireland. A trained facilitator external to the nursing home delivered the Family Carer Decision Support intervention. The Family Carer Decision Support intervention demonstrated statistical significant impact in reducing family carer decision uncertainty on establishing care preferences at the end of life and improved family carer satisfaction on quality of care [20]. This implementation study proposes to; a) expand the Family Carer Decision Support intervention into nursing homes; b) extend its application internationally; and, c) train nursing home staff to deliver the Family Carer Decision Support intervention rather than a trained external facilitator.

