## Methods/design

### Design

This research will employ a multiple case study design where a nursing home will be the unit of analysis or ‘case’ [21, 22]. A case study design will allow us to understand the implementation process for the Family Carer Decision Support intervention and to identify the factors which determine how well the intervention will work. We will use a formative design, generating hypotheses about the mechanisms that will lead to successful implementation, testing and refining these hypotheses by introducing the intervention into the nursing homes sequentially (where possible). A sequential approach will allow the experiences and learning from implementing in the first wave to influence implementation approaches taken in the second wave.

The RE-AIM framework will guide the evaluation [23–25]. A major feature of RE-AIM is that it shifts the focus from effectiveness trials to longer-term effectiveness in a real- world setting. The dimensions of the framework are as follows:Reach, the proportion and representativeness of identified nursing home staff and family members who access the online training resource and review resource featuresEffectiveness, the impact the advance care planning intervention has on staff and family members knowledge, decisional conflict and attitudes towards the intervention and advance care planningAdoption, assess nursing home staff acceptability of the training and family members impression of the suitability of the information resourcesImplementation, assessment of the fidelity of implementing the protocolMaintenance, determine whether nursing home managers and staff wish to continue the intervention

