## Discussion

### Strengths

The protocol takes into consideration social distancing and other relevant Covid-19 infection prevention and control practices. Although this study is not directly focused on the context of the Covid-19 pandemic, the timing of the study means that it will take place when levels of Covid-19 infection could well be significant in each national context. On this basis, we will provide resources/tools and equip nursing homes, their staff, residents and family members during a time when developing an end-of-life care plan or advance care plan has never been more pressing for people.

The research builds on previous evidence of the effectiveness of the Family Carers Decision Support intervention and through a multiple case study design will evaluate the intervention in different national, regional, cultural, social and organisational contexts.

While it is hoped that the intervention resources will impact on policy and practice in the nursing homes that are recruited to the study, the development of implementation guidelines will ensure impact on wider national policy and practice. It is our aim that the resources will be sustainable beyond the duration of the study and this will enable the resources to have a longstanding relevance for future advance care planning practice for staff, family carers and residents with advanced dementia.

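### Pooled, uncontrolled scores set against the earlier Northern Ireland trial can describe, but cannot determine, how the new way of implementing compares with the old

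*Protocol article*

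**What the plan says.** In Data management and analysis the article states: "we will compare the pooled outcome measure data from the current adapted Family Carer Decision Support intervention to the outcome measure data" of the "earlier cluster randomized control trial involving 24 nursing homes located in Northern Ireland". The next sentence draws the inference: "This will determine how the adapted implementation approach for scaling up the intervention compares to the original implementation approach". No caveat, adjustment, restriction to similar homes or common comparator is attached. The same section limits the analysis of the Decisional Conflict Scale (DCS) and the Family Perceptions of Care Scale (FPCS) to descriptive statistics, used to support the interview findings.

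On the current study, the Design section says: "This research will employ a multiple case study design where a nursing home will be the unit of analysis". No control homes are described. Under Phases 2 and 3, both scales are completed before the family care conference and again about 6 to 8 weeks later. Case sampling and selection gives 16 sites in six countries, chosen for their diversity.

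On the earlier study, the Background says that it "employed a cluster randomized control trial involving 24 dementia care nursing homes located in Northern Ireland" and that an external facilitator delivered the intervention. In the current study home staff deliver it. The Strengths section expects a period in which "levels of Covid-19 infection could well be significant in each national context". The limitations section discusses Covid-19 and remote delivery, but does not connect either with this comparison.

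**The concern.** The sentence promises a comparative conclusion about two ways of implementing the intervention. Several other things change at the same time as the implementation approach, and nothing in the current study shows what would have happened to the scores without the intervention. A difference from the earlier trial, or the lack of one, could therefore come from the period, the setting, the type of home or ordinary drift in the scores.

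The Objectives include assessing the impact of the new model of delivery on carers and staff, and this is the only stated quantitative comparison of the two approaches. If the sentence stands, change that has nothing to do with implementation could be credited to the adapted approach or held against it.

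**Working it through.** **Site count (the plan's own figure).** Canada 2 + Republic of Ireland 2 + UK 3 × 2 + Netherlands 2 + Italy 2 + Czech Republic 2 = 16 homes in six countries. This agrees with the article. Homes outside the UK: 10/16 = 62.5%. Homes in the Netherlands, Italy or the Czech Republic: 6/16 = 37.5%.

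**What differs between the two data sets.**

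| | Earlier trial, intervention arm | Current study |
|---|---|---|
| Who delivers | External facilitator | Home staff |
| Period | Earlier (date not given) | Later, Covid-19 expected |
| Setting | Northern Ireland | Six countries, four languages |
| Homes | Dementia care nursing homes | Nursing homes with 24-hour nursing care, deliberately diverse |
| Concurrent control | Yes, randomised | None |

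**Can the approach effect be identified?** Code delivery as 0 (external) or 1 (staff), and period as 0 (earlier) or 1 (current). Every earlier intervention record is (0, 0) and every current record is (1, 1). The two columns are identical, so only the sum of the delivery and period effects can be estimated. Setting overlaps in part at most: six homes are in the UK, but whether any is in Northern Ireland is not stated. Pooling all homes does not use that overlap.

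**What the missing control does.** Let E be the effect of the intervention and N the change that would have occurred anyway.
- Current change = E(new) + N(current).
- Earlier intervention-arm change = E(old) + N(earlier).
- Difference = [E(new) − E(old)] + [N(current) − N(earlier)].

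The earlier control arm estimates N(earlier). Nothing in either study estimates N(current).

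**Illustration on assumed inputs.** The article gives no SD, intraclass correlation (ICC), carer numbers or arm sizes. Assume 12 of the 24 earlier homes had the intervention, m = 3, 5 or 10 carers per home in both studies, and a true approach effect of zero. With design effect DE = 1 + (m − 1) × ICC, the effective numbers are 12m/DE and 16m/DE.

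*Chance that a pure non-implementation shift of b SD is nominally significant (two-sided 5%), ICC 0.02 to 0.10:*
- Smallest case, m = 3, ICC 0.10: DE = 1.2, effective numbers 30.0 and 40.0, standard error √(1/30 + 1/40) = 0.242 SD. For b = 0.3: 0.3/0.242 = 1.24, probability 0.24.
- Largest case, m = 10, ICC 0.02: DE = 1.18, effective numbers 101.7 and 135.6, standard error 0.131 SD. For b = 0.3: 0.3/0.131 = 2.29, probability 0.63.
- Full ranges: b = 0.2, 13% to 33%; b = 0.3, 24% to 63%; b = 0.5, 54% to 97%.

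The rate rises with sample size, so more carers would not cure the problem.

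*Precision if there were no bias at all.* Half-width of the 95% interval for the difference in mean DCS change = 1.96 × SD × √[DE × (1/(16m) + 1/(12m))], assuming an SD of change of 15 to 20 points and ICC 0 to 0.10.
- SD 15, m = 10, ICC 0: 29.4 × √(1/160 + 1/120) = 29.4 × 0.121 = 3.6 points.
- SD 20, m = 3, ICC 0.10: 39.2 × √[1.2 × (1/48 + 1/36)] = 39.2 × 0.242 = 9.5 points.

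**The case against.** The strongest reply is that this is a secondary benchmark in a descriptive case study. No test, margin, sample size or decision rule depends on it. The main analysis works case by case and then across cases, with the scores entered in each site's template, and the guidance is to take account of cultural and health-system differences. A full protocol or analysis plan may add detail. All of this stands, and it lowers the weight of the point. It does not rescue the sentence: descriptive statistics cannot determine the matter, and no later analysis plan can separate delivery from period or supply a concurrent control.

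Several stronger readings are tempting, but the article does not support them:
- *That the comparison is of internal with external delivery alone.* The text compares two implementation approaches as packages. The Background lists international extension beside staff delivery, so country and language are arguably part of the package. Period and the missing control remain problems on either reading.
- *That a single-arm change will be set against a between-arm effect.* The text refers to outcome data collected in the trial, which could mean the intervention arm alone.
- *That the earlier trial was pre-pandemic or conducted in English.* The article says only that it was earlier and in Northern Ireland.
- *That external facilitators blur the contrast by joining conferences.* The Internal facilitators section has them there only as non-participant observers; their feedback and debriefing belong to the adapted model.
- *That equivalence will be claimed.* No such claim is planned. Misreading a null result is a risk to guard against.

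**Conclusion.** The point holds as one about the stated conclusion. The comparison may be made, but it cannot determine how the two approaches compare. This follows from the design and needs no assumed figure: delivery agent and period are completely aliased, setting and home type differ, and change in the current homes has no concurrent control.

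The size of any bias cannot be derived from the article. The 24% to 63% false-attribution range for a 0.3 SD shift, and the 3.6 to 9.5 point half-width, rest on assumed carer numbers, ICC, arm split and, for the second, SD. They show only that a modest unrelated shift could pass for a finding and that a null result may be uninformative. The sentence should be corrected before results are interpreted. The rest of the study does not depend on it.

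**What to change.** In Data management and analysis, replace the opening *This will determine how* with *This will describe, without attributing differences to the implementation approach, how*. Then add:

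1. The quantity compared is change from baseline, set against the earlier trial's intervention-arm change. The control-arm change is shown alongside as an approximate benchmark for non-specific change. It is approximate because it belongs to another period and setting.
2. Results are shown by country as well as pooled, with 95% confidence intervals that allow for clustering by home. Five of the six countries have only two homes, so country intervals will be wide.
3. Absence of a difference is not evidence of equivalence.

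A UK-only contrast and baseline-adjusted mixed models are optional. Under the assumptions above, a contrast using the six UK homes has a half-width of about 4.6 (29.4 × √(1/60 + 1/120)) to 12.4 points (39.2 × √[1.2 × (1/18 + 1/36)]), and it leaves delivery and period aliased.

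The cost is a weaker stated conclusion and a little more analysis, provided the earlier trial's results by arm are available to the team. No new data collection is needed.

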### Ethical and governance issues

To minimise participant burden, the total duration of interviews will be limited to a maximum of 60 min. Interviews will be undertaken by experienced researchers in the field of nursing home research.

Participation will incur time and some interviews may cover emotional and distressing issues. Participation is voluntary and any participant can choose to end their involvement in the study without needing to give a reason why. However, we also anticipate several benefits from taking part in this study. It is anticipated that nursing home staff and family members will be more knowledgeable and feel more prepared in having advance care plan conversations.

Involvement in the study will be kept confidential. Participant information will only be accessible to members of the research team. Personal information will be coded with a unique identifier number (a number linked to participants name which only the research team will have access to on an encrypted file). We will keep all information safe and secure on Microsoft Teams (GDPR compliant), and participants’ identities will be anonymised in any publications or other outputs. Digital recordings will be deleted as soon as the transcript is transcribed. All information will be treated as strictly confidential and handled in accordance with GDPR.

### Dissemination and knowledge, transfer and exchange activities

It is envisaged that the study will produce a number of outputs, including: news media; digital media targeted at different stakeholders (such as family members, nursing home staff, policy makers, researchers and academics); conference presentations and webinars; open access publications in academic journals. Implementation guidance will also be written to guide researchers, healthcare staff and policymakers who may wish to implement this intervention or similar in the future.

The guidance will provide coherent and complex information about the most effective way of implementing Family Carer Decision Support intervention in nursing homes, taking into account cultural and health care systems differences across countries.

Communication is a central pillar of this project in respect of implementation delivery and the intervention focus. On this basis, we will develop and implement a knowledge transfer, exchange (KTE) and communication plan and support and develop early career researcher’s in dementia and palliative care research. The knowledge exchange and dissemination plan will be informed by an Evidence-based Model for the Transfer and exchange of Research Knowledge for palliative care research [32]. The plan will outline the content to be communicated to nursing home sites and wider resources to disseminate (end of project outputs, short term outcomes, and long-term impact), map the stakeholders (internal and external); define potential benefits and KTE strategy for early career researchers. The knowledge exchange and communication plan will include the following activities: developing a project website, establishing an early career research committee to share learning across partner countries, a mentoring scheme for early career researchers and knowledge exchange committee to plan activities, develop study newsletters, design project logos and branding.

## Discussion

### Strengths

The protocol takes into consideration social distancing and other relevant Covid-19 infection prevention and control practices. Although this study is not directly focused on the context of the Covid-19 pandemic, the timing of the study means that it will take place when levels of Covid-19 infection could well be significant in each national context. On this basis, we will provide resources/tools and equip nursing homes, their staff, residents and family members during a time when developing an end-of-life care plan or advance care plan has never been more pressing for people.

The research builds on previous evidence of the effectiveness of the Family Carers Decision Support intervention and through a multiple case study design will evaluate the intervention in different national, regional, cultural, social and organisational contexts.

While it is hoped that the intervention resources will impact on policy and practice in the nursing homes that are recruited to the study, the development of implementation guidelines will ensure impact on wider national policy and practice. It is our aim that the resources will be sustainable beyond the duration of the study and this will enable the resources to have a longstanding relevance for future advance care planning practice for staff, family carers and residents with advanced dementia.

### Limitations, challenges and further opportunities

Should this project need to be implemented and delivered using remote and online methods due to Covid-19 restrictions, this is likely to impact on the delivery of the project. This is both a potential limitation, but also an area of interest given that implementing and delivering remotely and online may highlight novel approaches which will make considerable additions to the literature on advance care planning and implementation research in this wider field. Given the intervention will be implemented in six countries, remote and online delivery may be a factor or variable in some contexts and not others. This offers interesting and different implementation contexts, and is congruent with a multiple case study design which will allow us to understand the implementation process for the intervention and to identify the factors which determine how well the intervention will work.

This study will prompt further innovative research on advance care planning and staff education in nursing homes in the context of Covid-19. For example, UK based members of this project team and other colleagues have secured funding for a UK based project that will develop advance care plan training and informational resources for nursing home staff and family carers in the context of Covid-19 [33, 34].

## Abbreviations

CSRI: Client Services Receipt Inventory
DCS: Decisional Conflict Scale
FAST: Functional Assessment Staging Test
FPCS: Family Perceptions of Care Scale
RE-AIM: Reach, Effectiveness, Adoption, Implementation, Maintenance Framework
